### Sample size calculation

The sample size was based on RCT that compared the effectiveness of face-to-face home rehabilitation to conventional care after hip fracture of geriatric patients [64]. The home rehabilitation group showed a higher degree of recovery in self-care using the FIM, (calculated effect size: d = 0.8). The minimum sample size at the significance level of 5% (one-sided test) and power of 80% is 25 in each group. Estimated drop-out rate is 20%; therefore, a maximum of 30 participants will be recruited for each group.

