### Data analysis

Quantitative data will be analyzed using SPSS 21.0. Descriptive statistics will be obtained on the demographic, social and clinical pretest characteristics of subjects in the three groups. Differences in these variables between the intervention and control groups will be examined using either chi-square tests or analysis of variance. Feasibility in the research groups will be calculated according to the of participants who complete the trial.

Repeated-measures MANOVA will be used to test the effects of the group assignments (intervention vs. control), the effects of time (baseline, post-intervention, and 6-month follow-up), and the group-by-time interaction for measuring all the outcomes. Repeated-measures MANOVA is recommended as being straightforward, powerful, and appropriate to treatment outcome investigations [79]. In addition to providing a multivariate analysis of the effect of treatment on the combined changes in all measures and healthcare costs, this approach also provides a univariate analysis of the effect of treatment on each measure, thus allowing an investigation of which measures were most affected by treatment [79]. *p*-Values less than 0.05 are considered to be statistically significant in all comparisons.

All qualitative interviews (patients and caregivers) will be video/audio-recorded and transcribed. Conventional content analysis with constant comparative methods will be used for coding and analysis. All data will be collected anonymously, and access will be restricted to the investigators.

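### The sample-size paragraph labels its test one-sided, but 25 per group is the two-sided answer and no one-sided test is planned

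*Protocol article*

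**What the plan says.** The Sample size calculation section of the protocol article bases the size on an earlier randomised trial that "compared the effectiveness of face-to-face home rehabilitation to conventional care after hip fracture of geriatric patients", and takes from its FIM self-care result a "calculated effect size: d = 0.8". It continues: "The minimum sample size at the significance level of 5% (one-sided test) and power of 80% is 25 in each group". It then assumes 20% drop-out and concludes that "a maximum of 30 participants will be recruited for each group".

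The Data analysis section plans a repeated-measures MANOVA with group, time and group-by-time effects, followed by univariate results for each measure. Baseline differences are examined by chi-square tests or analysis of variance. For significance, p-values "less than 0.05 are considered to be statistically significant in all comparisons". That section names no directional test. The one-sided label appears only in the sizing paragraph.

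**The concern.** All inputs to the calculation and its result stand in one paragraph, so the result can be checked directly, and it does not reproduce. The label also has no counterpart in the analysis: MANOVA, analysis-of-variance and chi-square tests of these effects have no direction. When a single contrast is tested by an F-test with one degree of freedom, its p-value is the two-sided t-test p-value.

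At stake is a clear statement of the error rate behind the design. A reader who takes the label literally reconstructs a different sample size and power from a reader who follows the Data analysis section. Sidedness should be fixed in writing before the data are analysed. An unseen analysis plan could state the sidedness of the analysis, but it could not make 25 the one-sided answer for d = 0.8.

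**Working it through.** **Inputs.** From the Sample size calculation section: d = 0.8, alpha 5%, one-sided, power 80%, stated n = 25 per group, 30 recruited per group, 20% drop-out. I assume a comparison of two equal groups on a continuous outcome, because the effect size comes from such a comparison.

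**Formula (normal approximation).** n per group = 2(z_alpha + z_beta)² / d², with z_beta = 0.842 for 80% power and d² = 0.64.

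**1. As stated, one-sided 5%** (z_alpha = 1.645):
2 × (1.645 + 0.842)² / 0.64 = 2 × 6.185 / 0.64 = 19.3, so 20 per group. The noncentral t calculation gives 20.03, so 21 per group (power 81.7%). The stated 25 is not reproduced.

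**2. Two-sided 5%** (z_alpha = 1.960):
2 × (1.960 + 0.842)² / 0.64 = 2 × 7.851 / 0.64 = 24.5, so 25 per group. This matches the stated figure exactly. The noncentral t calculation gives 25.5, so 26 per group (power 80.7%). A one-sided 2.5% test gives the same 25 to 26.

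**3. Can another reading rescue the one-sided label?**
- *Rounding of d.* At d = 0.75, the smallest value that rounds to 0.8, the one-sided t-test needs 22.7, so 23. To have 80% power at exactly 25 per group, d would have to be about 0.71, which does not round to 0.8.
- *A rank test.* Dividing 20.03 by a relative efficiency of 0.955 to 0.864 gives 21.0 to 23.2, so 21 to 24 per group. Even the least favourable value falls short of 25, and no rank test is planned.

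**4. Power at the stated and expected numbers.** By the normal approximation, power = Φ(d√(n/2) − z_alpha).
- n = 25: 0.8 × √12.5 = 2.828. One-sided: Φ(2.828 − 1.645) = Φ(1.183). Two-sided: Φ(2.828 − 1.960) = Φ(0.868).
- n = 24 (30 × 0.80): 0.8 × √12 = 2.771. One-sided: Φ(1.126). Two-sided: Φ(0.811).

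| n per group | One-sided 5%, normal / t | Two-sided 5%, normal / t |
|---|---|---|
| 25 | 88.2% / 87.4% | 80.7% / 79.1% |
| 24 | 87.0% / 86.1% | 79.1% / 77.4% |

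Only the two-sided column agrees with 25 per group at 80% power.

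**5. What cannot be computed.** The article gives no correlations between outcomes or over time, so the power of the three-arm repeated-measures MANOVA cannot be derived. The figures above describe one comparison of two groups.

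**The case against.** The best defence is that only one word is out of place. The number, the power and the undirected 5% rule in the Data analysis section agree with one another once the label is ignored: 25 per group gives 79% to 81% two-sided power. Taken literally, the label makes the paragraph conservative, since one-sided power at 25 would be 87% to 88%. This defence stands, and it limits the weight of the point. It does not remove the inconsistency, because a stated minimum of 25 is wrong for the one-sided test that the sentence names.

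Two stronger readings are tempting, and the document supports neither.
- A reader might infer that the trial is underpowered because of the label. On neither reading of sidedness does the label cause a shortfall. Expected completers fall to 24 because of how drop-out was allowed for (25 × 1.2 = 30, where 25 / 0.8 = 31.25 would round up to 32). That is a separate matter.
- A reader might infer that benefit will be claimed at a one-sided 5% level, which doubles the false-positive rate in the favourable direction from 2.5% to 5%. Nothing in the Data analysis section plans to test one tail or halve p-values, and its MANOVA tests have no direction. The risk would arise only if the label were later carried into a pairwise comparison.

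It is also fair to say that relabelling aligns the error rate only. The calculation would still be for two groups and one outcome.

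**Conclusion.** The point holds as an internal inconsistency in the sizing statement. With d = 0.8, 80% power and a one-sided 5% test, the minimum is 20 to 21 per group and not 25, a gap of 4 to 5 per group. The figure 25 is the two-sided 5% result by the normal approximation, and 26 is the t-test result. As the planned tests are non-directional, the label is more likely wrong than the number. That is an inference, since the article does not show its calculation.

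The practical size is small. The label changes no recruitment target, test or threshold, and it does not make the trial too small. Once sidedness is corrected, the power to quote is the one at the expected 24 completers per group: about 77% (t-test) or 79% (normal), against the stated 80%. These figures assume d = 0.8, equal groups, exactly 20% drop-out in each group and a single two-group comparison at 5%.

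**What to change.** In the Sample size calculation section, replace one-sided with two-sided and name the method: for d = 0.8, two-sided 5% and 80% power, 25 per group by the normal approximation or 26 by the t-test. In the Data analysis section, add that tests are two-sided.

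Keep the enrolment of 30 per group and report what it delivers. After 20% drop-out, 24 per group are expected, which gives about 77% (t-test) or 79% (normal) power for a two-group comparison. The new text should not present 25 or 26 evaluable per group as what 30 enrolled will yield. It should also say that this power refers to one comparison of two groups and does not describe the three-arm MANOVA.

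The cost is two or three sentences and a quoted power slightly less favourable than 80%. Recruitment, the planned tests and the significance threshold stay as they are.

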### Trial design, randomization and recruitment

This study is a three-armed, evaluator-blind, randomized control trial (RCT) and will be implemented according to CONSORT guidelines [57]. Participants will be assigned to research and control groups by using a blocked randomized controlled design, stratified based on age. The randomization sequence will be computer generated and will be known only to the responsible investigator.

All participants will be recruited at the time of discharge from hospital. Health professionals employed at the hospital will screen and refer to a research assistant the interested clients who meet the inclusion criteria. The research assistant will obtain informed consent from caregivers and patients prior to randomization and trial inclusion. Participants (*n* = 90) will be randomized after baseline assessment in the three-arm study. The rehabilitation program will be identical in both intervention groups; only the delivery mode will differ: in-home telerehabilitation or face-to-face home visit. The patients allocated to all groups will continue to receive the standard usual care to improve adherence to intervention protocols. All outcomes will be measured at all three time points: Baseline-pretest (T0), immediately following intervention (post intervention 10 weeks) (T1), and a 6-month follow-up (T2) (See Fig. 1).

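### At the forecast 20% drop-out, 30 recruits per group leave 24, one short of the stated minimum of 25; the 80% power is missed only if that 25 is a two-sided figure

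*Protocol article*

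**What the plan says.** The protocol article's section on the sample size calculation takes a standardised effect from an earlier trial of home rehabilitation ("calculated effect size: d = 0.8", on the FIM). It then states: "The minimum sample size at the significance level of 5% (one-sided test) and power of 80% is 25 in each group". The next sentence deals with attrition: "Estimated drop-out rate is 20%; therefore, a maximum of 30 participants will be recruited for each group".

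The total agrees with this elsewhere. The section on trial design, randomization and recruitment says "Participants (*n* = 90) will be randomized after baseline assessment in the three-arm study". The abstract also gives 90, with 30 in each of the two intervention groups, which leaves 30 for the control group.

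No formula is shown for the 25 or for the step from 25 to 30.

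**The concern.** The section calls 25 a minimum, forecasts 20% drop-out, and presents 30 as what follows from the two. A recruitment number derived that way should leave at least 25 per group once the forecast loss has occurred, and 30 does not. Because 30 is worded as a ceiling, the text leaves no room to recruit a few more to reach the minimum.

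Completers matter here. The data analysis section plans a repeated-measures MANOVA over three time points, and as commonly run that method uses only participants with complete data. The article does not say how missing data will be handled, so this is an assumption. If it holds, the number left after drop-out is the number that carries the power.

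At stake is whether the stated power still applies at the stated drop-out, and whether a reader can judge the finished trial against a correct benchmark.

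**Working it through.** **Inputs**, all from the sample size section: d = 0.8; 5% significance, one-sided; power 80%; minimum 25 per group; drop-out 20%; 30 recruited per group. The total of 90 is from the trial design section.

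**1. Reproducing the 30.**
- Multiplying up: 25 × (1 + 0.20) = 30, exactly the stated figure.
- Dividing by the retained share: 25 / (1 − 0.20) = 31.25, rounded up to 32 per group, or 3 × 32 = 96 in total.

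The stated 30 is consistent with multiplication and not with division.

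**2. What 30 delivers.**
- Completers at 20% loss: 30 × 0.80 = 24 per group, or 72 in total against 3 × 25 = 75.
- Largest loss that still leaves 25: 1 − 25/30 = 16.7%, or 5 of 30.

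**3. Reproducing the 25.** With the normal approximation, n per group = 2(z_α + z_β)² / d².
- One-sided 5%: 2(1.645 + 0.842)² / 0.64 = 19.3, so 20. The t-test gives 20.03, so 21.
- Two-sided 5%: 2(1.960 + 0.842)² / 0.64 = 24.5, so 25. The t-test gives 25.5, so 26.

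The 25 does not follow from the one-sided test named in the same sentence. It does match a two-sided test.

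**4. Power at d = 0.8.**

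| Completers per group | One-sided 5%, t-test (normal) | Two-sided 5%, t-test (normal) |
|---|---|---|
| 25 | 87.4% (88.2%) | 79.1% (80.7%) |
| 24 | 86.1% (87.0%) | 77.4% (79.1%) |

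By t-test, the step from 25 to 24 costs 87.4 − 86.1 = 1.3 points one-sided and 79.1 − 77.4 = 1.7 points two-sided. With 24 per group, the effect detectable with 80% power is d = 0.73 one-sided and d = 0.83 two-sided.

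**5. Recruitment needed for 20% loss, by base number.**

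| Base per group | Where it comes from | Divided by 0.8 | Recruit per group |
|---|---|---|---|
| 21 | one-sided, t-test | 26.25 | 27 |
| 25 | as stated; two-sided, normal | 31.25 | 32 |
| 26 | two-sided, t-test | 32.5 | 33 |

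Thirty is enough in the first case and short in the other two.

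**The case against.** The strongest defence is that nothing of substance is lost. The section states a one-sided test, and under that test 24 completers per group give 86% power, above the 80% target. A correct one-sided base of 20 to 21 would need at most 27 recruits per group, so 30 would be ample. The 20% is only an estimate, and the gap is one person per group.

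Most of this stands. It removes two stronger conclusions that a reader might draw. One is that the trial falls below its stated power; for the test as written, it does not. The other is that enrolment must rise to 32 per group; that holds only if the 25 is the right base, and the 25 does not reproduce one-sided. Even on a two-sided reading, little of the cost comes from the drop-out step: by t-test, power is already 79.1% at the full 25.

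A reader might also take it as established that the 30 came from multiplying by 1.2. That is an inference. It gives 30 exactly, but the article shows no formula.

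A further defence is that the 25 might already include drop-out, since 20/0.8 = 25. The wording does not support this. The section ties the 25 to the significance level and power, and brings in drop-out only in the next sentence. If the 25 did include it, drop-out would have been counted twice and the section would still need correcting.

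The defence does not remove the internal contradiction: a stated minimum of 25, a stated loss of 20%, and a stated ceiling that yields 24.

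**Conclusion.** The contradiction is real and rests on the section's own three figures: 30 recruits with 20% loss leave 24 per group, one below the stated minimum, and 30 tolerates 16.7% loss rather than 20%. This does not depend on the sidedness of the test or on how the 30 was reached.

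The effect on power is small and does depend on sidedness. At d = 0.8 by t-test, 24 per group gives 86% one-sided, which meets the target, and 77% two-sided, which does not. The stated 80% is therefore missed only if the 25 is a two-sided figure, as its size suggests. These power figures assume a simple comparison of two group means at one time point, which is what the stated d, significance level and power imply, and they assume that only completers contribute. They do not describe the planned repeated-measures MANOVA itself.

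This is a correction to the stated justification. It is not a reason to regard the trial as too small.

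**What to change.** 1. **Settle the base first.** Confirm whether the calculation was one-sided or two-sided, and make the 25 and the stated test agree. Any change to the recruitment figure before that would build on a number that does not follow from its own inputs.
2. **Then restate the drop-out sentence and keep 90 in total.** Suggested content: 30 per group allows for 16.7% loss before falling below 25; at 20% loss, 24 per group remain; for d = 0.8 this gives 86% power at one-sided 5%, or 77% at two-sided 5%. Give only the figure for the confirmed sidedness, so that the paragraph does not contradict itself. If the confirmed base is no longer 25, recompute the tolerated loss as 1 − base/30.
3. **Drop the ceiling.** Replace "a maximum of 30 participants will be recruited for each group" with a plain target of 30 per group.

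The change costs one sentence and needs no extra participants. The downside is a slightly less favourable stated figure: a smaller drop-out allowance and, if the test is two-sided, a stated power just under 80%.

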## Discussion

This study has the potential to guide clinical practice toward innovative modes of rehabilitation care and enhance clinical management of hip fracture in older people. If efficacious, our results will provide a novel online delivery method that rehabilitation professionals can incorporate into their treatment program, which in turn will optimize outcomes. The proposed innovative telerehabilitation directly addresses one of the major issues of geriatric rehabilitative care – continuity. It is designed to support the weakest links in the chain of care transition [26]. It will assist in the transition from hospital to community dwelling, as well as maintaining the rehabilitation achievements. Since the hours of supervised therapy are limited, telerehabilitation will enable patients to expand significantly the hours that they practice therapeutic exercises [54], while promoting more effective methods of long-term rehabilitation and maintenance of a healthy lifestyle [80].

There are barriers to overcome relating to patients’ personal restrictions, staff logistical issues of the systems to ensure the implementation of telerehabilitation more widely in older adults [81]. However, community-dwelling older people who have received a home telerehabilitation program found telerehabilitation convenient and motivating, coped well with the technology, and developed positive therapeutic relationships [82]. In addition, the current research will allow examination of the cost-effectiveness of telerehabilitation in a large cohort of patients after hip fracture. The availability of this service will enable reduction of the length of rehabilitation hospitalizations, and will be used as an alternative to conventional ambulatory rehabilitation, particularly for those patients in rural and peripheral areas. Furthermore, this type of service is compatible with the evolving models of self-management, in which clients are encouraged to take responsibility for managing their diseases or impairments [83].

To summarize, three major innovations are presented in our suggested protocol: First, this protocol outlines the justification for the first RCT study in telerehabilitation service for patients after hip fracture. Second, our proposed service is based on available, easy-to-use, inexpensive, simple technology [46], using off-the-shelf applications. Last, the focus is on individualized day-to-day function rather than exercising, as an individualized approach may be most effective due to the patient's unique characteristics [84].

## Abbreviations

ADL: Activities of daily living
CO – OP: Cognitive Orientation to daily Occupational Performance
COPM: The Canadian Occupational Performance Measure
FIM: Functional Independence Measure
GDS: Geriatric Depression Scale
MOCA: Montreal Cognitive Assessment
QOL: Quality of life
RCT: Randomized controlled trial
SF– 12: 12-item MOS Short-Form Health Status Survey
ZBI: The Zarit Caregiver Burden Interview.
